**Assessments for Efficacy**

1. **Laboratory assessments**: Fasting serum samples will be drawn at baseline and every 3 monthly for the following analytes, lipid panel, leptin, adiponectin, and 25-hydroxyvitamin D. All samples will be spun in a centrifuge and the serum stored at -70 degrees in a freezer at the Division of Endocrinology, Department of Pediatrics, University of Massachusetts Medical School. Whole blood samples will be collected for HbA1c estimation. At the end of the study, all samples will be assayed simultaneously by the Umass Memorial Hospital Biochemistry laboratory. HbA1c, the primary efficacy parameter, will be assayed by the HPLC method. Its inter-assay variability is <1.5%, and intra-assay variability is <2.5%, with a normal range of 4.4.-6.0%. Lipid profile will be assayed by the Enzymatic method; leptin by Human Leptin ELISA kits developed by LINCOplex (Linco Research, St Louis, MO) (sensitivity 0.01 ng/mL, interassay coefficient of variation 5%; adiponectin by Human Adiponectin ELISA kits developed by B-Bridge International (San Jose, CA) (lower limit 0.02 ng/ml; interassay coefficient of variation 3.2%); and 25-hydroxyvitamin D by chemiluminescence assay. All remaining specimens will be disposed of 5 years after the study.
2. **Body mass index**: Using a wall-mounted stadiometer for height measurement, and an electronic scale for body weight measurement, these anthropometic measurements will be obtained at -3, 0, +3, +6 and +9 months. Measurements will be taken in triplicates and the average taken.
3. **Insulin dosing**: All participants will be on basal-bolus insulin regimen. Weekly weight-adjusted total daily doses of insulin will be collected on all participants to identify changes in insulin requirements during the study.

**Assessments for Safety**

**Hypoglycemia**: The major safety concern for this study, as in the general management of diabetes, is hypoglycemia. For this study, the following classification of hypoglycemia will be used: (a) **major**: hypoglycaemic event requiring a third party assistance, (b) **minor**: self measured plasma glucose level of ≤ 60 mg/dL, (c) **symptoms only**: self-measured plasma glucose of > 60 mg/dL or no measurement during the episode, (d) **nocturnal**: self-measured plasma glucose of ≤ 60 mg/dL occurring between 11 pm and 6 am. Hypoglycemia will be monitored by self-measured plasma glucose by checking blood glucose before meals, at bedtime, and at 3 a.m. We will evaluate the glycemic profile every third day by reviewing the data sent in to our office by the participants’ families via fax or email. Insulin dose adjustments, and other appropriated suggestions will be made based on these data. We will ensure that participants maintain a bedtime blood glucose level of >100 mg/dL before going to sleep. It is the standard of care for patients to check their blood sugar level before bed and if it is less than 100 mg/dL to eat a snack and recheck their blood sugar to make sure that it is over 100 before going to bed.

Participants will also check 3AM blood glucose twice weekly and also on 2 consecutive nights following changes to their long-acting insulin dose.

**Renal and liver function tests**: We will obtain liver function studies, and creatinine levels at the beginning and at the end of the study.

We will monitor **weight, body mass index, and vital signs** at each visit.

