**Table 3. Supplemental Insulin Dose Adjustment Plan**

| Prior meal Blood Glucose levels (mg/dL) | Current meal blood glucose level (mg/dL) | Supplemental Insulin dose (SID) |
| --- | --- | --- |
| greater than 130 | 80-130 | Interpretation: correct SID  Instruction: nothing to do |
| greater than 130 | less than 80 | Interpretation: SID is too high  Instruction: increase sensitivity factor by 10 |
| greater than 130 | greater than 130 | Interpretation: SID is too small  Instruction: decrease sensitivity factor by 10 |

**C. Basal Insulin adjustment plan:** Basal detemir injection will be given consistently at bedtime once a day. Subjects will titrate their long-acting insulin analog (detemir) dose every third day, to achieve a fasting plasma glucose of 90-120 mg/dL using the algorithm shown in Table 2 below. We will aim to maintain participants on a total daily **basal** insulin dose of 0.3-0.8 U/kg/day or higher if necessary, given once daily at bedtime. This will ensure relative normal inter-prandial glycemia and the achievement of our HbA1c targets.

**D. Metformin or Placebo:** All participants will be provided with a 3 month supply of metformin or placebo at baseline, +3, and +6mo. Subjects will be advised to start at one capsule daily for 2 weeks, and then increase to 2 capsules once daily for the remainder of the study duration.

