**Table 2. Titration Algorithm for Long-acting insulin analog (Detemir)**

| **Average FPG of 3 consecutive days** | **Recommended Long-acting insulin analog dose adjustments** |
| --- | --- |
| <90 mg/dL (5.0 mmol/L) | -2 units of detemir |
| 90-120 mg/dl (5.0-6.7 mmol/L) | No adjustments |
| > 120 mg/dL (>6.7 mmol/L) | +2 units of detemir |

**Follow up phone calls:** Subjects will be followed with twice weekly phone calls in the first month of enrollment to assess compliance and to help calculate insulin titration doses and make necessary dose adjustments. After the first month of study, subjects will be contacted every 2 weeks until the end of the study. We will also instruct the families to call the diabetes line during the first week of treat to target regimen if any fingerstick blood glucose reading is <70 mg/dL or two readings of >250 mg/dL.

**Downloading of Glucometer reading:**Each subject will be provided with a glucometer. They will be instructed on how to download the glucose readings to a computer. They will be advised to download their glucometer readings on every third day and email or fax the downloaded data to a contact number or email address provided by the investigators for review and a follow up recommendation.

All participants will return to the clinic at +3 and +6 months for interim visits and at +9 months for study conclusion.

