Treat to target regimen and oral medications will not be initiated simultaneously. Our protocol is to initiate and familiarize the patients with all aspects of treat to target regimen during the run-in phase of the study without adding metformin or placebo. Thereafter, we will introduce the oral agents. Therefore, subjects will have ample time to work with treat to target regimen before receiving oral agents.

We do not anticipate an increased frequency or risk of hypoglycemia with the treat to target regimen because treat to target regimen is not a unidirectional model of care. It is based on a bidirectional flexible model that allows the patient to subtract or add 1-2 units to his/her long acting insulin dose depending on his 3-day average fasting blood glucose level. We have also built in a close follow up and monitoring plan for this study. For example, the frequent phone calls during which we will review finger stick blood glucose readings with the family and the fact that the families will fax or email finger stick blood glucose readings to us twice weekly will ensure very close monitoring of blood glucose excursions throughout the study duration. We will also ensure that participants maintain a bedtime blood glucose level of >100 mg/dL before going to sleep. Participants will also check 3AM blood glucose twice weekly and also on 2 consecutive nights following changes to their long-acting insulin dose. We will also instruct the families to call the diabetes line during the first week of treat to target regimen if any fingerstick blood glucose reading is <70 mg/dL or two readings of >250 mg/dL.

We also do not anticipate the adjunctive metformin therapy to cause hypoglycemia as we will be titrating basal insulin doses to the prevailing glycemia, and will reduce the dose of basal insulin if there is evidence of incipient hypoglycemia.

Finally, we have included a Hypoglycemia Monitoring Table to enable participants document their low sugar reactions in an effective way so we can address these reactions promptly.

b. Explain what steps will be taken to protect against its occurrence, minimizing the harm, methods for early detection of harm, and what procedures will be followed to avoid serious injury (e.g. withdraw from study or dose reduction).

Study Safety Officer: [name].

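### The nocturnal hypoglycemia class leaves out unmeasured night events that needed assistance, and its detection depends on how often detemir is changed, so raw counts by arm may mislead

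*Protocol*

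**What the plan says.** All references are to the protocol.

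- **Classes (Assessments for Safety).** *Major* is an event needing help from a third party; no glucose value is required. *Minor* is a self-measured value of 60 mg/dL or less. *Symptoms only* is "self-measured plasma glucose of > 60 mg/dL or no measurement during the episode". *Nocturnal* is "self-measured plasma glucose of ≤ 60 mg/dL occurring between 11 pm and 6 am".
- **When glucose is checked (same section).** One sentence gives times without a frequency: "Hypoglycemia will be monitored by self-measured plasma glucose by checking blood glucose before meals, at bedtime, and at 3 a.m". A later one sets the 3 AM frequency: "Participants will also check 3AM blood glucose twice weekly and also on 2 consecutive nights following changes to their long-acting insulin dose". The risk section (item 8) repeats the second statement.
- **What changes the detemir dose (Visit III, part C, and the titration table).** "Subjects will titrate their long-acting insulin analog (detemir) dose every third day, to achieve a fasting plasma glucose of 90-120 mg/dL". A three-day mean below 90 or above 120 mg/dL moves the dose down or up by "2 units of detemir". On impending lows, the risk section adds: "we will be titrating basal insulin doses to the prevailing glycemia, and will reduce the dose of basal insulin if there is evidence of incipient".
- **What treatment is expected to do.** The general hypothesis is that metformin improves control more rapidly. H1B expects a larger fall in fasting plasma glucose on metformin. Total daily insulin dose is a secondary outcome.

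**The concern.** There are two linked problems.

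**Classification.** *Nocturnal* depends on a meter reading, not on when the event happened. A night episode in which the child needed help and nobody took a reading is among the most serious night events, yet it cannot enter the nocturnal class. The *symptoms only* wording meanwhile admits any episode without a measurement and does not exclude assisted ones, so the same event fits both the most and the least serious label.

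**Detection.** A nocturnal low has to be measured to count, and extra 3 AM checks follow each detemir change. Detemir changes are driven by fasting glucose, which metformin is expected to lower. The number of night checks is therefore a post-randomization variable. If one arm changes dose more often, its nights are searched more often, and it will show more nocturnal lows at the same true risk.

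The protocol calls hypoglycemia its major safety concern and says the trial will help determine metformin's safety profile. In a placebo-controlled trial, a table of nocturnal events will probably be read by arm.

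**Working it through.** The protocol states no hypoglycemia rate and no dose-change frequency, so there is no figure of its own to reproduce on this point.

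**1. The class definitions applied to a night episode (for example 2 am) that needed third-party help**

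| Class | No reading taken | Reading of 60 mg/dL or less |
|---|---|---|
| Major | yes | yes |
| Minor | no | yes |
| Symptoms only | yes, by the wording | no |
| Nocturnal | no | yes |

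The same episode enters or leaves the nocturnal class according to whether a meter was used.

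**2. Prescribed 3 AM checks per week**

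Inputs from the protocol: two routine checks per week, two further nights after each long-acting dose change, and a titration step every third day. Assumption: each step changes the dose, up or down, with probability p. The fraction of nights triggered by a change is then 2p/3.

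The protocol does not say whether triggered nights count toward the two weekly checks, so both readings are shown.

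- *Reading A, triggered nights count toward the two.* Checks are the weekly average of the larger of 2 and the number of triggered nights, simulated over 30,000 weeks. At p = 1 this is 7 × 2/3 = 4.67.
- *Reading B, two fixed nights apply in any case and may coincide with triggered nights.* Checks = 7 × (2p/3) + 2 × (1 − 2p/3) = 2 + 10p/3. At p = 1 this is 5.33.

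| p | A | B |
|---|---|---|
| 0 | 2.00 | 2.00 |
| 0.25 | 2.20 | 2.83 |
| 0.40 | 2.50 | 3.33 |
| 0.50 | 2.75 | 3.67 |
| 0.60 | 3.05 | 4.00 |
| 0.75 | 3.59 | 4.50 |
| 1 | 4.67 | 5.33 |

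**3. Ratio of checks between arms**

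If the risk of a low per checked night is the same in both arms, the ratio of lows found by these checks equals the ratio of checks.

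| Assumed p in the two arms | A | B |
|---|---|---|
| equal | 1.00 | 1.00 |
| 0.25 and 0.40 | 1.14 | 3.33/2.83 = 1.18 |
| 0.25 and 0.50 | 1.25 | 3.67/2.83 = 1.29 |
| 0.40 and 0.60 | 1.22 | 4.00/3.33 = 1.20 |
| 0.50 and 0.75 | 1.31 | 4.50/3.67 = 1.23 |
| 0 and 1 (bound) | 2.33 | 2.67 |

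**4. Effect on *minor* events**

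Pre-meal and bedtime checks dominate this class. Assuming three meals and one bedtime check a day, they give 28 checks per week. For p = 0.25 and 0.50 under reading B, the ratio is (28 + 3.67)/(28 + 2.83) = 31.67/30.83 = 1.03, so the effect is a few percent.

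**The case against.** Several points on the other side are sound.

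- **Other night readings count.** A reader might infer that only 3 AM lows qualify. The definition takes any self-measured value in the window, so symptom-driven checks count, as would a late bedtime or early breakfast reading. These pull the ratio of total nocturnal lows toward 1. The ratios above apply only to lows found by the prescribed 3 AM checks.
- **No arm difference is shown.** The rule is identical in two blinded arms, and changes in either direction trigger checks. Metformin could mean fewer upward steps or more downward ones. Of the two earlier trials described in the background, one found a lower insulin dose on metformin and the other no significant difference. A reader might conclude that metformin will look safer than it is; the documents do not support that direction, or any other.
- **No planned test is affected.** The statistical section lists no between-arm analysis of hypoglycemia, and the safety officer's list of items to review does not name nocturnal events. The choice of denominator could properly be left to a statistical analysis plan, which is not at hand.
- **The larger figures overstate the size.** The 2.33-fold ratio is a bound that compares a change at every step with none at all. Adding triggered nights to routine ones without overlap gives (2 + 2.33)/(2 + 1.17) = 1.37 for p = 0.50 and 0.25; allowing overlap gives 1.29.
- **The assisted night event is still counted as *major*.** It is not lost from safety reporting, and the protocol does not say that the classes exclude one another.
- **The two 3 AM sentences can be read together**, the first giving times and the second a frequency.

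Blinding and a common rule do not remove the dependence, because the trigger is itself an outcome of treatment. The class definitions are fixed in the protocol and misclassify as written, whatever a later analysis plan says.

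**Conclusion.** The point holds in a limited form.

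The classification defect follows from the wording alone: an unmeasured night episode needing assistance is *major*, literally also *symptoms only*, and never *nocturnal*.

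The detection problem is conditional. Raw nocturnal counts may not be comparable between arms if detemir is changed at different frequencies. The distortion is about 1.1 to 1.3 under the modest differences assumed here, and none if frequencies are equal. These ratios rest on assumed change probabilities, equal risk per checked night, and full adherence to the check schedule. A reader might go further and infer that the arms cannot be compared, or that the trial's safety conclusion is invalid. The documents establish neither, since they give no dose-change frequency and state no between-arm test of hypoglycemia.

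The remedy is cheap and worth making, but this does not threaten the primary analysis.

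**What to change.** Leave the 3 AM safety checks as they are. Change the definitions and the by-arm summary:

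1. Make *nocturnal* a time flag, 11 pm to 6 am, on any major or minor event, whether or not a reading was taken.
2. Limit *symptoms only* to events that did not need assistance.
3. In any by-arm summary of nocturnal hypoglycemia, report lows per night checked, taking the denominator from the meter downloads already sent every third day, or restrict the summary to the routine twice-weekly checks. Show the number of nights checked in each arm.
4. Reconcile the two statements on 3 AM checks, and say whether post-change nights count toward the two weekly checks. Without that, routine nights cannot be identified for the restricted summary.

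The cost is wording and a denominator, with no extra tests or visits. It assumes that the downloads carry time stamps and that the clock time of unmeasured events is recorded; the participants' hypoglycemia table could hold it.

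Neither summary is perfect. A per-check rate still mixes routine nights with post-change nights, whose true risk may differ. Restricting to routine checks avoids most of that but uses fewer readings.

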**3. VISIT III: BASELINE INTERVENTION STUDY VISIT AT O MO**

Following the screening study, qualified subjects will return to the Children’s Diabetes Service in the morning, after an overnight fast for initial intervention study blood draw. Anthropometric measurements: height, weight, waist circumference will be obtained. Vital signs and fasting glucose level will be checked. A venous catheter will be inserted in the antecubital fossa and blood sample will be drawn for fasting lipids, leptin, and 25-hydroxyvitamin D at baseline.

*Vital Signs:* Blood pressure and pulse will be measured using an electronic sphygmomanometer.

*Physical Examination:* Weight, height and waist circumference will be measured in all participants at baseline, 3 months and 6 months. Weight will be measured using an electronic scale with patient donning under-garments and a hospital gown. Values will be expressed to the nearest 0.1 kg. Height will be measured using a wall-mounted Harpenden stadiometer. Waist circumference will be measured at the level of the umbilicus, using a standard measuring tape. All measurements will be done in triplicates and the average taken. We will derive body mass index from the weight and height data.

*Blood samples:* At baseline, following an overnight fast, we will draw fasting blood samples for the following laboratory tests: lipid profile, leptin, adiponectin, hepatic function tests, serum creatinine, and 25-hydroxyvitamin D. These analytes will be redrawn at 3, 6 and 9 months. Only 2 teaspoons of blood will be drawn for these tests at each time point. All samples will be spun upon collection using a centrifuge and the serum collected and stored at -70 degrees until assay. Whole blood samples will be collected for HbA1c estimation.

Urine test: Urine pregnancy test will be obtained on all female participants and will be repeated at +3mo, and + 6mo.

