**6. RELATIONSHIP TO STANDARD THERAPY.**

Describe the standard therapy that patients would receive if not in the research study. Explain how this research intervention deviates from or replaces generally accepted standard therapy and justify the deviation.

Standard Treatment for Double Diabetes:

There is no consensus on the modalities of treatment for double diabetes in children and adolescents. Most endocrinologists would treat these individuals with insulin only. However, recent reports[43] now suggest that overweight adolescents with type 1 diabetes who are going through puberty would benefit from adjunctive therapy with agents that counteract the insulin resistance brought on by increased adiposity. Other studies have shown that patients with type 2 diabetes who possess diabetes-associated autoantibodies lose their beta cells faster than those without autoantibodies and thus will be dependent on insulin therapy sooner. Therefore, our study does not deviate from the emerging method of treating patients with double diabetes. Even though we cannot say that treat-to-target regimen is standard of care in children, the blood glucose targets we are using for age are defined by the American Diabetes Association. The only difference is that we have a dedicated staff that will follow up with the family to ensure compliance with the guidelines. Determir and aspart are standard of care.

RESEARCH INTERVENTION STUDY:

Eligible candidates will be required to receive either placebo or metformin 1000 mg daily. The follow up schedule and monitoring regimen are the same for other patients with diabetes.

The Research Study Protocol deviates from the Standard management of Double Diabetes:

- Quarterly blood draws for lipids, leptin, adiponectin, serum creatinine, hepatic function tests and 25OHD. The standard of care for blood draws is yearly blood draw for lipids, thyroid function tests, celiac antibodies, 25OHD, and quarterly blood draws for HbA1c.

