As the safety officer [name] will monitor participants in the study for adverse events related to the study drug, and make recommendations regarding removing subjects from the study or terminating the study if the incidence of adverse effects is significant.

He will review unblinded study data every month for the first 3 months of the study, and then every three months thereafter with regards to assignment of subjects to the study arms, prevalence of gastrointestinal side effects (including nausea, diarrhea and abdominal discomfort), unusual weight loss (>10% of body weight in 3 months), admissions to hospital or elevation of liver enzymes to >3 times above the normal limit. He will also review all other SAEs. This information will be forwarded to him by the study coordinator, and unblinding information by Investigational Drug Services which is responsible for blinding the study drug. He will perform this review every 3 months until the completion of the study. If an issue is found, he will report this promptly to the PI and will jointly issue an adverse effects or SAE report (as the case may be) with the PI to the UMass IRB and the study sponsor, Novo Nordisk Inc.

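### The safety officer's unblinded review does not name hypoglycaemia, the protocol's stated main risk, and the liver and creatinine schedule behind its liver item contradicts itself

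*Protocol*

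**What the plan says.** **Main risk.** Assessments for Safety states: "The major safety concern for this study, as in the general management of diabetes, is hypoglycemia". It then defines major, minor, symptoms-only and nocturnal events.

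**Unblinded review.** Section 8 gives the safety officer the task of recommending removal of subjects or termination of the study. On timing it says: "He will review unblinded study data every month for the first 3 months of the study, and then every three months thereafter". Besides arm assignment, the items are "prevalence of gastrointestinal side effects (including nausea, diarrhea and abdominal discomfort), unusual weight loss (>10% of body weight in 3 months), admissions to hospital" and "elevation of liver enzymes to >3 times above the normal limit", plus all other serious adverse events. The coordinator forwards this information, and the Investigational Drug Services supplies the unblinding.

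**Liver and creatinine tests.** Assessments for Safety says: "We will obtain liver function studies, and creatinine levels at the beginning and at the end of the study". Section 6, listing departures from standard care, says: "Quarterly blood draws for lipids, leptin, adiponectin, serum creatinine, hepatic function tests and 25OHD". The Summary of Procedure and Visit III also place both tests at baseline and at 3, 6 and 9 months.

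**Sample handling.** The Visit III blood list includes hepatic tests and creatinine and is followed by: "All samples will be spun upon collection using a centrifuge and the serum collected and stored at -70 degrees until assay". Assessments for Efficacy says: "At the end of the study, all samples will be assayed simultaneously".

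**The concern.** The safety officer's review is the only unblinded safety check that the Protocol describes, in a double-blind trial of participants aged 10 to 18 who titrate insulin while taking blinded capsules. If its list leaves out the risk that the Protocol ranks first, a difference between arms in non-serious hypoglycaemia could build up without anyone being assigned to look for it. Section 8 says that metformin is not expected to cause hypoglycaemia because basal insulin will be titrated to the prevailing glucose. That is an expectation, and counts by arm would test it.

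The liver-enzyme item raises a different problem. The officer can act on it only if values are measured and reported while participants are on capsules, and the sections disagree on whether any such test is scheduled before the last visit.

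**Working it through.** No sample size, power or error rate is involved. The check sets the sections side by side and counts scheduled tests.

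**1. Does hypoglycaemia reach the officer by arm?**

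- *Named items (Section 8):* gastrointestinal effects, weight loss, admissions, liver enzymes. Hypoglycaemia is not among them.
- *All other serious adverse events:* hypoglycaemia that is serious or leads to admission does reach the officer. The text shown does not say that every event needing third-party assistance counts as serious. Minor and nocturnal events are defined by a self-measured glucose of 60 mg/dL or less, so many would not be serious.
- *General remit:* this covers adverse events related to the study drug. Section 8 lists hypoglycaemia as a risk of insulin, so events could be attributed to insulin and fall outside the remit.
- *Glucose review every third day (Assessments for Safety):* this serves individual dose adjustment. Type of Trial says that physicians are blinded to the oral agent, so this review cannot show an imbalance between arms.
- *Withdrawal Criteria:* increasing hypoglycaemia is listed without a threshold and applies to one participant at a time.

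Non-serious events without admission therefore have no assured comparison by arm.

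**2. Scheduled liver and creatinine tests on capsules before +9 months**

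| Place in the Protocol | +3 | +6 | Count |
|---|---|---|---|
| Assessments for Safety | no | no | 0 |
| Summary of Procedure (Section 4) | yes | yes | 2 |
| Visit III, blood samples | yes | yes | 2 |
| Section 6 | yes | yes | 2 |
| Visit IV, anthropometric paragraph | yes | yes, as Visit V is identical | 2 |
| Visit IV, blood-samples paragraph | omitted | omitted, as Visit V is identical | 0 |

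The difference is 2 − 0 = 2 tests per participant. With a count of 0, the officer's liver item has no scheduled on-treatment value until that participant's +9-month visit.

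**3. Are these tests frozen and batched?**

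- *For:* at Visit III they stand in the list that the freezing sentence follows, and that sentence covers all samples. The batch sentence in Assessments for Efficacy also refers to all samples.
- *Against:* the Assessments for Efficacy paragraph names lipids, leptin, adiponectin, 25-hydroxyvitamin D and HbA1c, but neither hepatic tests nor creatinine. Visit VI describes the hepatic and renal tests after its freezing sentence, gives them an additional teaspoon of blood, and compares them with screening and monitoring results. Visit I uses liver and kidney results for enrolment, and Other steps to minimize harm requires liver tests before metformin starts.

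The wording is ambiguous, and the weight of the text is against batching these tests.

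**The case against.** The strongest reply is that participants are closely protected. Families send in glucose data every third day, calls are twice weekly and later every two weeks, 3 a.m. checks and a hypoglycaemia monitoring table are in place, and families are told when to call the diabetes line. Serious events and admissions reach the officer unblinded. What is missing is an aggregate table of non-serious events.

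That reply stands as far as it goes. It shows that individuals are monitored, but blinded monitoring of individuals does not compare arms.

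A reader might infer that the review is built to miss its main signals and would look clean whatever happened. The documents do not support this: admissions, liver enzymes and all other serious adverse events are on the officer's list.

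A reader might also infer that liver and renal results are held until the study ends, so that no review would see any. That needs the batch sentence to cover tests that its paragraph does not name, and it conflicts with Visit VI and with the use of screening results. Even under the beginning-and-end schedule, if enrolment is staggered over the 24-month study, final values from participants who have finished would reach later reviews.

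Creatinine is not a named item for the officer, so the schedule conflict bears on that review only through liver enzymes.

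**Conclusion.** Two points hold on the text. First, hypoglycaemia is not a named item in the unblinded review, so events that are neither serious nor lead to admission have no assured comparison by arm. This assumes that no fuller listing for the safety officer exists outside the document, and that not every event needing assistance is classed as serious. Second, the liver and creatinine schedule contradicts itself across sections and within Visit IV. The size is 0 against 2 scheduled on-treatment tests per participant before +9 months.

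The freezing wording is a third, lesser point: an ambiguity to clear up, not a stated plan to withhold safety results.

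This should be fixed because it bears on participant safety. It does not affect the primary analysis.

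**What to change.** - **Section 8, safety officer's review:** add counts of hypoglycaemia by arm, using the classes already defined in Assessments for Safety and the glucose and event data already collected.
- **Liver and creatinine schedule:** reconcile the Summary of Procedure, Visit III, both paragraphs of Visit IV, Visit V, Assessments for Safety and Section 6. Which schedule applies is for the investigators to decide.
- **Visit III and Assessments for Efficacy:** state that hepatic and creatinine tests are outside the frozen end-of-study batch and are reported as they arise.

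The cost is wording, one additional table for each review, and routing of results. The glucose downloads already exist, and the quarterly blood draws take place under either reading of the liver and creatinine schedule. No clinical threshold is proposed.
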